**2.3. Secondary Objective(s) and Hypotheses**

The secondary objectives, for the secondary endpoints described in paragraph 2.4 below, aim to: (1) show an impairment of these criteria in the study's children with CP compared to typically developing (TD) children; (2) show a significantly greater improvement in these criteria after 3 months of RAIT than after 3 months of RH; (3) show a further improvement in these criteria when the duration of RAIT is increased.

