**3.2.3. Sample Size Calculation**

The calculation of the number of subjects needed is based on the primary endpoint. The distribution of the peak sternum deceleration at the beginning of the stance phase was Gaussian in our previous study. On average, this distribution was centered on 3.0 ± 1.1 m.s-2 (mean ± 1 standard deviation) in children with CP and on 1.1 ± 0.3 m.s-2 in TD children (24). The expected effect of RAIT is a minimum reduction in the peak sternum deceleration at the beginning of the stance phase of one-third of its value, similar to the effect of RAIT in the previous study (24). To demonstrate an effect of RAIT using a repeated measures ANOVA in which we expect a small effect size, with an alpha level set at 0.05 and a power of 80%, a total sample size of 24 patients, i.e., 12 per group, is necessary (calculation performed using G*Power 3.1 software; **Figure 3).** We expect greater variability in dynamic gait variables (expected in children aged 18 months to 5 years and 6 months compared to children aged 5 to 12 years). Therefore, we plan to recruit 32 children with CP (16 per group), to account for this greater variability and to compensate for potential dropouts.

[figure not shown]

**Figure 3:** Calculation of the number of subjects needed, performed using G*Power 3.1 software.

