**3.4. Experimental Plan**

The project includes a clinical examination and instrumental functional explorations at four time points. The experimental plan is shown in Figure 4. The assessments are described in chapter "4.3. Measurements – Description of assessments performed during the research." Assessments will be conducted at M0, M3 (M0 + 3 months), M6 (M0 + 6 months), and M12 (M0 + 12 months) for children with CP and at M0 for TD children. Thus, three rehabilitation periods will be planned: the first between M0 and M3, the second between M3 and M6, and the third between M6 and M12. A first group of children (group PC1) will continue their usual rehabilitation (RH) for the first 3 months and then will have RAIT for the following 9 months (PC1 = RH-RAIT). The second group of children, PC2, will immediately have RAIT for the 12 months of the study (PC2 = RAIT-RAIT). As the previous study conducted in children with CP aged 5 to 12 years showed a therapeutic effect only related to RAIT (and not to RH), RAIT will be continued for the children who benefited from it from the first 3-month period and for all children for the last 9 months of the study. Such a plan will allow to: 1) ensure that all children with CP benefit from RAIT; 2) measure the effect of RAIT over 3 months compared to that of RH; 3) test the reproducibility of the effect of RAIT over 3 months between the two groups and 4) test the effect of an additional 3 months of RAIT in the PC2 group (M6 versus M3) and 6 months in both groups (M12 versus M6) (**Figure 4**).

[figure not shown]

**Figure 4:** Experimental plan of the study. RAIT: rehabilitation through postural activities involving the trunk; conventional rehabilitation is based on the treatment of muscle groups (stretching, strengthening, tone reduction) of the lower limbs

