**4.5. Statistical Analysis Plan**

Statistical analyses will be performed using general linear models, as the overall sample size (N=64) and the size of each group (n=32) are considered sufficient for applying such procedures. The conditions for using these tests will be verified beforehand, particularly the normal distribution of residuals (using quantile-quantile plots and Shapiro-Wilk tests) and the homogeneity of variance (Levene's tests). If the data do not meet these conditions, non-parametric equivalents will be used.

In the first phase, the group effect (Children with CP vs. TD Children) will be analyzed using multivariate analysis of variance (MANOVA) procedures on the dependent kinematic (step width), dynamic (sternum and L5 decelerations and anterior foot position during the 1st double-support phase), and clinical (ECAB, GMFM-66-IS, and "Reaching Hand" questionnaire) variables. A multiple linear regression analysis will also be performed, with the anterior foot position during the 1st double-support phase as the dependent variable and the sternum and L5 decelerations at the beginning of the stance phase as the regressors.

Furthermore, the effects of the specific rehabilitation (2 Groups x 4 Periods) will be tested using the same type of multivariate procedures (MANOVA) and a 2 Groups [PC1 vs. PC2] × 4 Periods [M0, M3, M6, M12] mixed design, with a particular focus on the Group × Period interaction. If this interaction is significant, the analysis of local comparisons using post-hoc procedures (Tukey's tests) will allow us to examine: 1) the significance of the rehabilitation (significant difference between the two groups at M3 with a reduction in the peak sternum deceleration at the beginning of the stance phase for the group that underwent RAIT between M0 and M3); 2) the reproducibility of the RAIT effect (similar differences between M3 and M6 for the RH-RAIT group and between M0 and M3 for the RAIT-RAIT group); and 3) the enhancement of the RAIT effect when it is continued (between M6 and M0 versus between M3 and M0, and between M12 and M0 versus between M6 and M0 for the RAIT-RAIT group; and between M12 and M3 versus between M6 and M3 for the RH-RAIT group).

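### The M6 to M12 continuation question is examined only after a significant Group × Period interaction, to which a gain shared by both groups contributes nothing

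*Protocol*

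**What the plan says.** - **Objective.** Section 2.3, third secondary objective, for the endpoints of section 2.4: "show a further improvement in these criteria when the duration of RAIT is increased".
- **Design.** Section 3.4 lists among the aims a test of "an additional 3 months of RAIT in the PC2 group (M6 versus M3) and 6 months in both groups (M12 versus M6"). It also states that RAIT is given "for all children for the last 9 months of the study", so from M6 to M12 no group is without it.
- **Model.** Section 4.5 specifies multivariate procedures on a 2 Groups × 4 Periods "mixed design, with a particular focus on the Group × Period interaction".
- **Condition.** Section 4.5 continues: "If this interaction is significant, the analysis of local comparisons using post-hoc procedures (Tukey's tests) will allow us to examine" three items. The third is the enhancement of the RAIT effect when it is continued. For the last six months, the comparison named in PC2 is "between M12 and M0 versus between M6 and M0 for the RAIT-RAIT group". The one named in PC1 is "between M12 and M3 versus between M6 and M3 for the RH-RAIT group".

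No contrast averaged over the two groups is named, and no continuation question is tied to the Period main effect, although the 2 × 4 design yields one.

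**The concern.** An interaction test asks whether the two groups follow different courses over the visits. Objective 3, for the stretch from M6 to M12, asks whether children improve further while all of them receive the same treatment. An equal improvement in both groups is the natural expectation, and the interaction cannot see it. The plan therefore makes the answer to one question depend on the significance of another.

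This matters most if RAIT acts slowly, with a modest difference at 3 months and more later. The interaction is then least likely to be significant, and objective 3 would usually not be examined at all. A report of no further improvement could then mean only that the comparison was never made.

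**Working it through.** **1. The plan's own figure.** Section 3.2.3 gives 24 children for a repeated-measures ANOVA at alpha 0.05 and 80% power. Figure 3 is not shown, so I assume the within-between interaction option with r = 0.5 and no sphericity correction. With f = 0.25: λ = f²·N·m/(1−r) = 0.0625 × 24 × 4/0.5 = 12, df 3 and 66, power 0.816. N = 24 is reproduced. The calculation sized the interaction or an equivalent within-child test. It was not made for M12 versus M6.

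**2. What the listed comparisons are.** (M12−M0) − (M6−M0) = M12−M6 within PC2. (M12−M3) − (M6−M3) = M12−M6 within PC1. Each is a before-after change in one group of 16.

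**3. Why the shared gain cancels.** Let the 3-month RAIT effect be δ, with PC1 catching up at M6, and let the further gain be g in both groups. Means at M0, M3, M6, M12:
- PC1: 3, 3, 3−δ, 3−δ−g
- PC2: 3, 3−δ, 3−δ, 3−δ−g
- PC1 − PC2: 0, δ, 0, 0

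g is absent from the difference, so it is absent from the interaction. This needs no numerical assumption and holds equally for a multivariate interaction.

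**4. Inputs for the size.**
- From section 3.2.3: "centered on 3.0 ± 1.1 m.s-2 (mean ± 1 standard deviation) in children with CP and on 1.1 ± 0.3 m.s-2 in TD children", giving SD 1.1; δ = one-third of 3.0 = 1.0; 16 per group.
- Assumed, because the protocol does not give them: r = 0.3/0.5/0.7, equal between all visits; no dropout; a univariate interaction F test; g; and the Tukey family, either all eight group-by-visit cells or the four visits.

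**5. Chance that the condition is met.** The centred differences have sum of squares 0.75δ². The within-child error is 1.21(1−r) = 0.847/0.605/0.363. So λ = (16/2) × 0.75δ²/error, with df 3 and 90.

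| δ | λ at r = 0.3/0.5/0.7 | Condition met |
|---|---|---|
| 1.0 | 7.08 / 9.92 / 16.53 | about 57 / 74 / 93% |
| 0.5 | 1.77 / 2.48 / 4.13 | about 17 / 23 / 36% |
| 0 | 0 | 5% |

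g does not appear in the formula. Simulation gives the same chances whether g is 0 or 1.0.

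**6. Slow-acting case, δ = 0.5 and g = 1.0.** Simulated detection in at least one group (eight-cell Tukey) is about 15/21/36%. The same Tukey tests without the condition give 73/90/99%. Repeat runs agree to within about two points. Here the condition alone hides a large gain.

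**7. Planned case, δ = 1.0 and g = 0.5, at r = 0.5.** Smallest M12−M6 change that is declared significant:
- Per group, Tukey over eight cells: 4.39 × √(0.605/16) = 4.39 × 0.1945 = 0.85
- Per group, Tukey over four visits: 3.70 × 0.1945 = 0.72
- Pooled over 32 children: 2.04 × √(2 × 0.605/32) = 2.04 × 0.194 = 0.40

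A true gain of 0.5 lies below both Tukey thresholds and above the pooled one. Simulated detection:

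| Route | r = 0.3 | 0.5 | 0.7 |
|---|---|---|---|
| Conditional, per group, eight cells, at least one group | 9% | 16% | 39% |
| Conditional, per group, four visits, at least one group | 18% | 31% | 59% |
| One unconditional contrast pooled over both groups | 56% | 70% | 89% |

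At r = 0.5, dropping the condition alone raises the first row only from 16% to 20%.

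**8. Larger gains, δ = 1.0, eight cells, at least one group.** g = 0.75: 44% at r = 0.5 and 82% at r = 0.7. g = 0.9: 61% and 92%. A gain of 0.9 would bring the mean from 2.0 to the TD value of 1.1.

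**The case against.** - **The protocol does not promise a single pooled test.** A reader might infer one from section 3.4, but testing in both groups can equally mean in each group, and section 4.5 takes it that way. This stands: the two sections do not contradict each other here, and pooling is a choice of efficiency. The mismatch with the interaction remains under either reading.
- **A reader might infer that a real gain will mostly be missed.** That depends on a gain, a correlation and a Tukey family that the protocol does not give. With δ = 1.0, a 0.75 gain at r = 0.7 is found in over 80% of trials even with eight cells.
- **The interaction condition is not the main obstacle in the planned case.** With the planned δ it is usually met, and most of the loss comes from splitting by group and the Tukey correction. It becomes decisive when the M3 difference is small.
- **The figures are not for objective 3's own endpoints.** Objective 3 concerns section 2.4, which does not include peak sternum deceleration, and no SD is given for any endpoint there. Section 4.5 also specifies MANOVA. The percentages are therefore illustrations; the cancellation does not depend on them.
- **A pooled M12−M6 change is not a RAIT effect.** All children receive RAIT in that period and they are young, so maturation cannot be separated from treatment. This stands and limits what any version of the comparison can show.
- **The cancellation covers M12−M6 only.** A further M3 to M6 change in PC2 is not shared in the same way and can enter the interaction.

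**Conclusion.** The point holds in limited form. Section 4.5 makes the M6 to M12 continuation question conditional on a test that is insensitive to the shared gain being sought, and whether the question is reached depends on the M3 group difference. That conclusion rests on the protocol's text and on algebra.

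Its size rests on the assumptions in step 4. After a modest 3-month effect of 0.5, a further gain of 1.0 is found in about 15/21/36% of trials, against 73/90/99% without the condition. After the planned effect of 1.0, a 0.5 gain is found in 9–18%, 16–31% and 39–59% at r = 0.3, 0.5 and 0.7, depending on the Tukey family. One pooled contrast finds it in 56/70/89%. The loss is small for large gains at high correlation when the 3-month effect is as planned. The primary RAIT-versus-RH comparison at M3 is outside this point. A correction should be made, but it concerns a secondary, uncontrolled comparison.

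**What to change.** In section 4.5:
1. Take the third item (enhancement with continued RAIT) out from under the interaction condition.
2. Pre-specify, for the section 2.4 endpoints and for the primary variable if wanted, two contrasts: M12−M6 averaged over PC1 and PC2, and M6−M3 in PC2. Estimate each from the repeated-measures model with a 95% confidence interval, whatever the interaction shows.
3. Report the group-specific M12−M6 changes as descriptive.
4. Label all of these as before-after changes that cannot be separated from maturation.
5. Keep the Group × Period interaction for questions about differences between the groups.

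The cost is wording only: no added visits, data or children. The downside is that these secondary contrasts each carry their own 5% error, which the text should say.

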**4. Conduct of the Research**

**4.1. Child Recruitment Procedure**

The Center for Physical Medicine and Rehabilitation for Children (CMPRE) in Flavigny-sur-Moselle is a regional center providing various functional assessment and treatment services for children with orthopedic, neurological, or neuro-orthopedic abnormalities, including children with CP. Functional motor assessment sessions are offered and include clinical assessments (neuro-orthopedic evaluations and functional motor scores) and functional explorations of walking and standing using a pressure-sensitive walkway, video cameras, and inertial measurement units.

The initial diagnosis and medical follow-up of children with CP are carried out by physicians interacting in different settings: RAFAEL network (Lorraine Family Support Network), neuro-pediatric consultations at the Brabois Children's Hospital in Vandœuvre-lès-Nancy, Early Medico-Social Action Centers (CAMSP) in Lorraine, private pediatric consultations, or consultations at the Center for Physical Medicine and Rehabilitation for Children in Flavigny-sur-Moselle. The solicitation of these different physicians across Lorraine should allow for the inclusion of 32 children with CP over a 30-month period.

When one of these physicians, during a consultation with a child with CP, prescribes a functional motor assessment associated with a medical consultation at the CMPRE and this child is potentially eligible for the study, they will orally inform the parents in an interactive exchange and give them the information sheet and consent form in preparation for a possible inclusion in the study, if they agree. When scheduling the appointment at the CMPRE, the contact information of the physical therapist who treats the child will be collected so that he or she can be informed about the study and their consent to participate can be obtained, in case of the child's inclusion.

During the medical consultation associated with the child's functional motor assessment, one of the recruiting physicians from the CMPRE ([name], [name], [name]) will explain the study to the parents and the child, according to their level of understanding, based on the documents in their possession during an interactive exchange and will offer them to participate if the eligibility criteria are met. If they agree, they will sign the previously provided consent form, and their child's inclusion in the group with initial RAIT or in the group with initial usual rehabilitation will be allocated according to a prior randomization. If the parents wish to think further before accepting or refusing their child's participation in the study, an additional period of 7 days will be offered.

For the control group of TD children, recruitment will be done through an email announcement presenting the study and including the information and consent form, addressed to people in the Greater Nancy Metropolitan Area, within the staff of the University of Lorraine not hierarchically linked to the study investigators, or whose children attend sports and educational associations. The typically developing siblings of the children with CP participating in the study will also be solicited. Like the children with CP, they will be seen in consultation with an investigator physician. During this consultation, the investigator will be responsible for informing the participant and their parents about the nature of the study, its objectives, its methodology, its duration, the expected benefits, the foreseeable constraints and risks including in case of stopping the study before its term, and the medical care arrangements planned at the end of the research if necessary. This informative discussion will be based on the information letter previously provided to the parents.

The parents (and the participating child, within the limits of their young age) will have every opportunity to ask any questions concerning the research and will be informed of their right to refuse to participate in the research or to withdraw their consent at any time without prejudice and without having to justify the reasons for their decision. The children and their parents will be informed orally in understandable language about the course of the study and the examinations to be performed. The informed consent form will be signed in two copies by the different parties, after an additional reflection period if the parents so desire. The investigator and the parents of the child participating in the research will each keep an original copy of the consent form. The information for parents and any other written information given to them must be updated if new data becomes available that could change their opinion or if an amendment to the protocol requires a correction of the information and consent form. The investigator will inform the child's parents of these changes and ask them to confirm their agreement by dating and signing a new consent form. Any modification of these documents must be approved by the CPP.

**4.2. Rehabilitation Content**

Each child with CP will continue to participate in one to three rehabilitation sessions per week for a total of 12 months (initially 3 months of URor RAIT, then 9 months of RAIT) under the direction of the child's physical therapist, provided that he or she agrees to participate in the team and has not participated in the previous study using RAIT. The physical therapist is then initially informed of the principles of RAIT and receives detailed instructions on its content shortly before the start of the RAIT treatment period. For children who are treated at the CMPRE in Flavigny-sur-Moselle, a physical therapist from the center will be responsible for monitoring the patient's rehabilitation. Each session lasts about 30 to 45 minutes, and the child must receive exercises to be performed daily at home for 15 to 30 minutes, depending on the parents' availability.

Usual Rehabilitation corresponds to the type of rehabilitation the child was already receiving before the study; most often, it combines in varying degrees muscle stretching and strengthening, muscle tone reduction (e.g., neurodevelopmental treatment according to the Bobath concept), and therapist-facilitated training of upper and lower limb motor skills. These therapies, involving limited groups of muscles in stretches or elementary actions, usually target the muscles of the lower limbs, sometimes those of the upper limbs, and more rarely those of the trunk. During the study's UR period for the PC1 group, the physical therapist will propose to the parents, according to their availability and ability, to perform a suitable selection of the stretches and elementary actions that he or she performs in the office on the child daily for 15 to 30 minutes.

The RAIT program is not based on strengthening elementary trunk muscles, but on improving postural control and balance of the whole body, including the trunk and other affected muscles, by means of actions performed autonomously by the child in intermediate postures involving the trunk (24). Thus, the principle of this approach is, during autonomous actions in intermediate postures, to exploit the fundamental automatic control of postural support and balance to improve the use of affected muscles in support and balance not only during these actions but also during all postural and locomotor tasks, an original approach proposed for the rehabilitation of stroke patients (44). The child must control their balance during various voluntary actions, from intermediate postures such as repeatedly alternating between the four-point kneeling posture and the so-called "cobra" posture, or swinging the body back and forth from the so-called "downward-facing dog" posture (see **Figure 5**). These autonomous actions are less difficult than standing and walking, but beneficial effects on the latter are expected. From intermediate postures, the child also performs more difficult trunk movements, requiring the dissociation of the movements of the shoulder and pelvic girdles or a reduction of lumbar lordosis. The upper and lower limb rehabilitation goals defined before the study and followed during UR (e.g., hamstring stretches, plantar flexor stretches, and wrist extension) are included in some of the RAIT activities. For example, from a four-point kneeling position with wrists in extension, the child lifts the knees, which achieves hamstring and plantar flexor stretches while engaging the trunk and the whole body to manage balance. Finally, each child receives a selection of activities to be performed daily at home.

C

B

A

**Figure 5:** Examples of postural activities involving the trunk: repeatedly alternating between the four-point kneeling posture (A) and the so-called "cobra" posture (B); swinging the body back and forth from the so-called "downward-facing dog" posture (C). The images were not kept due to the lack of parental consent.

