Due to the importance of trunk control on the gross motor function, balance, and walking of children with CP, and given all the studies showing the benefit of a trunk-focused rehabilitation, trunk-focused rehabilitation protocols are now prescribed to patients in our center whose profile seems to indicate an interest in trunk strengthening. The study of the effect of RAIT on the ability to stabilize in an unstable sitting position and on the dynamics of the trunk and ankle during walking, which we conducted, was carried out in children with CP aged 5 to 12 years, partly due to technical limitations related to the unstable seat and the three-dimensional motion analysis with many markers to be placed on the skin, which are difficult to perform on children under 5 years of age. However, it seems relevant to carry out a rehabilitation like RAIT early, from the age of 18 months, to improve postural balance control and walking dynamics in children with CP.

With this in mind and to simplify the functional exploration of walking dynamics, and to be able to evaluate the effects of the RAIT prescribed to our youngest patients, we have acquired inertial measurement units to measure the deceleration of the sternum and the sacrum (L5) and a pressure-sensitive walkway (**Figure 2**) to analyze gait instability via spatio-temporal parameters and to measure, at the beginning of the stance phase, the extent of the early forward shift of the plantar pressure associated with the toe-walking pattern. The analysis of postural control of standing is also simplified through the use of an inertial measurement unit placed at L5 to estimate the displacements of the body's center of mass (mSway software). Clinical scores are also used for an assessment of balance and global functional motor skills. Furthermore, RAIT has other potential benefits such as an improvement in the functional use of the upper limb and hand, observed on the sidelines of the study in children aged 5 to 12 years (24). Also, in this study we explore the motor function of the upper limb and hand via a questionnaire addressed to the parents.

[figure not shown]

**Figure 2:** Walkway equipped with relative pressure sensors (Zeno®) allowing for an extended and simplified analysis of spatio-temporal parameters and the dynamics of plantar footprints

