**3.2.1. Inclusion Criteria**

**For children with CP:**

- Age between 18 months and 5 years and 6 months
- CP of spastic diplegia or spastic hemiplegia type, GMFCS I to II
- No or moderate contracture of the triceps surae (ankle dorsiflexion: > 5° during clinical examination, knee extended)
- Sufficient level of understanding to perform the activities involving the trunk in the form of self-exercises (rehabilitation protocol) as well as the clinical assessments and functional explorations.
- Acceptance of the physical therapist in charge of the child's follow-up to collaborate in the implementation of the RAIT
- Affiliated with a social security scheme

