**5.2. Risks and Constraints for the Participant**

There are no major risks for the participant concerning the treatments and assessments performed. The postural activities, in which muscles and tendons are stretched, could initially be painful. However, any muscle and tendon pain, should it occur, would be mild and temporary because the stretching of muscles and tendons will be progressive, especially since the child performs the postural activities themselves.

The constraints related to the study are quite significant. The RAIT postural activities or, where applicable, a suitable selection of exercises related to usual rehabilitation prescribed by the physical therapist, must be performed regularly, every day, for at least 15 to 30 minutes (in one or more sessions). The home sessions are complementary to those performed with the physical therapist. An adult will need to be present during home sessions to supervise the child. The postural activities or usual rehabilitation exercises performed by the child at home will be recorded in a logbook so that their progress can be monitored by the physical therapist and the CMPRE team. There will be a total of 4 sessions at the CMPRE: at the start of the study and then at 3, 6, and 12 months. Each session will last several hours (2 to 4 hours) spread over one day and will include the motor function assessment and a medical consultation to review the postural activities. A member of the CMPRE team will contact the parents via teleconsultation once or twice between each motor function assessment at the CMPRE to answer their questions.

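### Therapists of PC1 children are told the principles of RAIT before delivering the M0-M3 usual-rehabilitation period, and those trained within this trial are not barred: a dilution risk of unknown size

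*Protocol*

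**What the plan says.** Protocol section 4.2 places each child's rehabilitation under that child's own physical therapist, "provided that he or she agrees to participate in the team and has not participated in the previous study using RAIT". It then describes when the therapist learns about the method: "The physical therapist is then initially informed of the principles of RAIT and receives detailed instructions on its content shortly before the start" (meaning when RAIT begins). Neither sentence separates PC1 from PC2. For children treated at the centre, "a physical therapist from the center will be responsible for monitoring" the rehabilitation.

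Other sections fix the timing and the setting:

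- Section 3.2.1 makes it an inclusion criterion, in both arms, that the therapist accepts "to collaborate in the implementation of the RAIT".
- Section 4.1 has the therapist's contact details "collected so that he or she can be informed about the study" when the appointment is made, which is before allocation.
- Section 3.3 randomises individual children, not therapists. Section 4.7 gives 30 months of inclusion.
- Section 3.4 has PC1 continue RH for the first 3 months and then receive RAIT for 9 months, while PC2 receives RAIT throughout.
- On the content of RH, section 4.2 says: "Usual Rehabilitation corresponds to the type of rehabilitation the child was already receiving before the study".
- Section 1 reports that "trunk-focused rehabilitation protocols are now prescribed to patients in our center" whose profile suggests a benefit.

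**The concern.** The protocol delays the detailed content of RAIT and excludes therapists from the previous RAIT study. It gives no reason, but both rules have the effect of limiting what the therapist knows about RAIT during RH. Two gaps remain.

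1. The principles are given at the start to every therapist, including one about to deliver three months of RH to a PC1 child. Section 4.2 describes them as autonomous actions by the child in intermediate postures that engage the trunk. A practising therapist could act on that without the detailed instructions.
2. The bar does not cover therapists trained in this trial. With allocation by child over 30 months, someone trained for a PC2 child, or for a PC1 child after M3, could later deliver RH to a new PC1 child.

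At stake is the comparison that carries the primary objective, namely that RAIT and not RH lowers peak sternum deceleration. If RH takes on elements of an effective RAIT, the difference at M3 shrinks. The sample-size section allows for greater variability and for dropout, but not for this.

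**Working it through.** **Step 1. Is M0-M3 the only randomised contrast?** Section 3.4 gives RH to PC1 from M0 to M3 and RAIT to both arms afterwards. Section 4.5 names the PC1-PC2 difference at M3 as the first post-hoc comparison. So yes.

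**Step 2. The protocol's own sample size.** Section 3.2.3 states 24 children (12 per group), alpha 0.05, power 80%, repeated measures ANOVA. The text does not give the remaining inputs. Assume a group-by-period interaction with k = 2 groups, m = 4 visits, f = 0.25, correlation rho = 0.5 and no sphericity correction.

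- Noncentrality: lambda = f^2 x N x m/(1 - rho) = 0.0625 x 24 x 4/0.5 = 12.
- Degrees of freedom: (k - 1)(m - 1) = 3 and (N - k)(m - 1) = 66.
- Power = 0.816, and 24 is the smallest even N that reaches 80%. The stated figure is reproduced under these assumptions.

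**Step 3. Effect of a leak.** Section 3.2.3 gives a mean of 3.0 and SD of 1.1 m/s2 in children with CP, and an expected reduction of one-third: 3.0/3 = 1.0 m/s2. Let c be the share of the RAIT effect that RH picks up.

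- Remaining contrast: 1.0 x (1 - c).
- Required n is proportional to 1/contrast^2, so it rises by 1/(1 - c)^2. At 10%, 1/0.81 = 1.23. At 20%, 1/0.64 = 1.56. At 30%, 1/0.49 = 2.04.

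**Step 4. Power.** For the M3 contrast, use a two-sided t test at 0.05 with 16 per arm, unadjusted for baseline. The noncentrality is (contrast/1.1) x sqrt(16/2); with no leak this is 0.909 x 2.828 = 2.57 on 30 degrees of freedom. For the ANOVA, keep the Step 2 assumptions with N = 32 and f scaled to 0.25 x (1 - c).

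| Leak c (assumed) | Contrast, m/s2 | Inflation of n | M3 power, 16 per arm | n per arm for 80% (t test) | ANOVA power, N = 32 |
|---|---|---|---|---|---|
| 0 | 1.0 | 1.00 | 0.70 | 21 | 0.92 |
| 10% | 0.9 | 1.23 | 0.61 | 25 | 0.85 |
| 20% | 0.8 | 1.56 | 0.51 | 31 | 0.75 |
| 30% | 0.7 | 2.04 | 0.41 | 40 | 0.62 |

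The t-test n grows slightly less than the inflation factor because of the small-sample correction. The 0.70 with no leak is a separate matter from contamination; only the fall from it belongs here.

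**Step 5. What is not known.** The protocol gives no leak fraction, number of therapists, share of children treated at the centre, or overlap of therapists between arms. The table illustrates sensitivity and does not predict what will happen.

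**The case against.** The strongest reply is that the protocol already limits the problem, and much of this stands:

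- Detailed RAIT content is held back until shortly before the RAIT period.
- RH is tied to what the child already received.
- The PC1 home programme consists of stretches and elementary actions that the therapist already performs in the office (section 4.2).
- Home exercises are logged and can be followed by the therapist and the centre team (section 5.2), so drift at home could be seen.
- Knowing a principle is not the same as delivering a structured daily programme.
- Children are recruited through physicians across a region and mostly keep their own therapist, so overlap between arms may be rare.

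These points reduce the risk but do not remove it. The logbook covers home exercises, and the protocol describes no equivalent record of office sessions. No rule keeps a therapist to one arm.

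Two stronger readings are tempting and are not supported.

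*That PC1 families are taught RAIT at M0.* Section 5.2 says each centre session "will include the motor function assessment and a medical consultation to review the postural activities", and a reader might infer that PC1 is included at M0. But that section describes participant burden, and the same paragraph twice refers to RAIT activities or usual-rehabilitation exercises as alternatives. The phrase is better read as shorthand covering all four sessions. Sections 3.4 and 4.2 govern what PC1 receives.

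*That a null result could not be told apart from contamination.* PC1 is measured at M0 and M3, and section 4.5 compares its M3-M6 change with the M0-M3 change in PC2. No M0-M3 improvement in either arm would argue against contamination. Improvement in PC1 during RH would point towards it, though development at this age could also explain it. The patterns are therefore partly distinguishable.

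**Conclusion.** The point holds as a design risk, not as a demonstrated bias. As written, section 4.2 lets a PC1 therapist deliver RH from M0 to M3 knowing the principles of RAIT, or fully trained through another child. If RAIT works, leakage moves the only randomised RAIT-versus-RH contrast towards no difference. It threatens power and the claim that RH lacks the effect; it does not inflate the type I error.

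The size cannot be derived from the protocol. The 10-30% range is assumed, and so are f, rho, the two-sided test and the transfer of the SD of 1.1 from the previous study's older children. On the protocol's own ANOVA as reproduced here, a 10% leak leaves power at 0.85 with 32 children, so a small leak is tolerable there. At 20% it falls to 0.75. A reader might also infer that the centre's therapists will treat both arms, but the protocol does not say so.

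The change is worth making before enrolment. It is cheap, and exposure that is neither prevented nor recorded during M0-M3 would be hard to reconstruct afterwards.

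**What to change.** In section 4.2:

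1. **Before allocation**, give therapists only the general information needed to agree to collaborate: two rehabilitation approaches are compared, and every child receives RAIT at some point. The information cannot differ by arm here, because sections 3.2.1 and 4.1 require agreement while the arm is still unknown.
2. **After allocation**, give PC1 therapists both the principles and the detailed content of RAIT only once the M3 assessment is done. PC2 therapists receive both at the start of their RAIT period.
3. **Extend the existing bar**: where another therapist is available, one already trained in RAIT within this trial does not deliver the M0-M3 RH period of a PC1 child.
4. **Where none is available**, record the exposure in the case report form and pre-specify a sensitivity analysis of the M3 contrast without those children. The full randomised comparison stays primary, because leaving out children from PC1 alone departs from the randomisation.

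The cost is protocol wording and one case report form field. Therapists commit on less information, and the sensitivity analysis uses fewer children. The treatments, visit schedule and sample size are unchanged.
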